## Abstract

**Background:**

Glioblastoma (GB) remains one of the most aggressive brain tumors, with limited survival and high recurrence rates. In most cases, GB recurrence occurs locally, either on the residual tumor after surgery or within 2 cm of the resection cavity—but in rarer cases, tumor cells can spread beyond this margin, leading to distant recurrence. By *spread*, we refer to the spatial dissemination of tumor cells beyond the typical local site, which can involve distant brain regions or even the leptomeninges, significantly impacting treatment planning and surgical decision-making. This study proposes the application of Machine Learning (ML) and Deep Learning (DL) approaches to MRI data from GB patients in the preoperative phases, aiming to develop predictive models to predict the extent of recurrence spread, on the integrated analysis of clinical, imaging, and instrumental data. Additionally, we plan to design a (semi) automatic segmentation tool for tumor delineation in MRI, which will support both the implementation of the study and serve as a standalone instrument to standardize volume measurement in neuroimaging.

**Methods and analytics:**

A multicenter retrospective collection of clinical and radiological variables will be performed for all eligible GB patients. Variables will include demographic, surgical, pathological, and preoperative MRI features. Predictive modelling will use classical ML algorithms (e.g., Random Forest, SVM, Multilayer perceptron, etc.) and a 3D U-Net architecture for DL-based image segmentation. Dimensionality reduction (PCA, LASSO, etc.) will be used to prevent overfitting and improve model generalizability. Model performance will be assessed through Area Under the Curve (AUC), P-R curve, F-score, accuracy, sensitivity, specificity, confusion matrix, and Dice score for segmentation.

**Discussion:**

The development of Artificial Intelligence (AI)-based predictive models for GB is expected to provide a major contribution to outcome prediction, early targeted interventions, and personalized care. These tools may support optimized resource allocation, reduce healthcare costs, and improve patient and family outcomes. The findings from this study will serve as a foundation for a future prospective multicenter validation study.

## Introduction

Glioblastoma (GB) is a highly infiltrative and aggressive neoplasm with a very poor prognosis and a high propensity of recurrence (1, 2). Despite multidisciplinary therapy approaches that include maximal safe resection followed by radiotherapy and chemotherapy, a long-lasting local tumor control cannot be achieved in most GB patients (3, 4).

A key challenge lies not only in detecting recurrence but in anticipating its spatial distribution, with an eventual distant spread. The location of recurrence is generally unpredictable and influenced by multiple factors, including surgical resection margins, as well as biological heterogeneity of the GB. In most cases, local recurrence within 2 cm of the resection cavity is inevitable. Brain tumors, including GB, rarely recur at anatomically distant sites; rather, they tend to exhibit a progressive spatial spread from the original tumor bed, extending beyond the immediate surgical margins. By *spread*, we refer to the gradual infiltration of tumor cells into adjacent or more distant brain regions, beyond the typical local recurrence zone. Therefore, it is the pattern of tumor cell dissemination, rather than the occurrence of isolated distant relapse, that would be most valuable to predict, as it ultimately determines the site and extent of recurrence in relation to the previous surgical cavity.

The choice between subtotal and gross total resection should be carefully tailored based on the lesion’s location, particularly whether it involves eloquent brain areas such as motor pathways, language areas, or other critical structures, in order to minimize the risk of postoperative or delayed neurological deficits. Additionally, the surgical approach is primarily guided by meticulous preoperative planning, which includes accurate anatomical localization of the tumor. Intraoperative neuromonitoring further informs surgical decisions, along with the prediction of the recurrence’s site, which can influence both the extent and trajectory of resection. Given the prognostic and therapeutic implications, particular attention should be paid to the precise anatomical localization of the predicted relapse. Predicting the site of recurrence — particularly whether it will occur locally, at the site of residual tumor or distally — is crucial for surgical planning as well as for successive oncological treatments. Knowing in advance where a recurrence is likely to occur allows the neurosurgeon to adopt a more extensive and aggressive resection strategy during the initial surgery, thereby improving the chances of local disease control (5–7). This consideration becomes especially relevant in cases where recurrence tends to arise within the same anatomical compartment or along resection margins. Moreover, predicting and precisely localizing tumor recurrence can significantly impact radiotherapy planning. If recurrence is expected beyond the tumor bed—the usual target of adjuvant irradiation—expanding radiation fields or adjusting treatment volumes may be warranted. Emerging evidence supports that personalized radiotherapy strategies can improve therapeutic outcomes.

In this context, there is a growing need for tools capable of forecasting the direction and extent of tumor spread. Recent advances in Artificial Intelligence (AI), particularly traditional Machine Learning (ML) and Deep Learning (DL), have demonstrated potential in supporting medical data analysis (2). These approaches aim to develop predictive models that integrate clinical, surgical, and imaging data to anticipate specific outcomes, guide therapeutic decisions, and improve patient management (8, 9).

In recent years, ML-based methods have been increasingly applied to the study of GB (2). However, to the best of our knowledge, they have not yet been successfully employed to predict the spatial pattern of GB spread, which would represent a critical step toward pre-emptive and personalized therapeutic planning.

Moreover, accurate and reproducible delineation of tumor volumes on MRI is a critical prerequisite for both model training and clinical decision-making. Therefore, alongside the development of predicting models, we will design and validate a semi-automatic segmentation tool based on a 3D U-Net architecture, to standardize tumor volume measurement and support downstream AI analyses.

## Methods and analysis

### Study design

This retrospective study will be conducted at different Italian Units of Neurosurgery for clinical data and images acquisition, with all ML and DL analyses performed at the Department of Physics and Chemistry of the Università of Palermo (Italy) and the Department of Mathematics and Physics of the University of Salento (Italy).

The project unfolds in two successive phases spanning a total of 24 months (Figure 1). During the first 6 months, we will secure all necessary administrative approvals and ethics committee clearances, complete team training, and assemble the retrospective clinical and imaging dataset. At the same time, we will define the key instrumental parameters for prognostic feature extraction, establish standardized protocols for data handling and quality control, and design software architecture to support subsequent ML and DL workflows.

**Figure 1 fig1:**
[figure not shown]
Gantt chart outlining the 24-month project timeline and task allocation. Key activities include: administrative and ethics clearance; research training; retrospective data collection; definition of prognostic parameters and data-management protocols; software system design; development and validation of manual and semi-automated MRI segmentation tools; implementation of Machine Learning and Deep Learning classification frameworks; statistical integration of methods; overall analysis, manuscript drafting, and result dissemination; and recurring project meetings. Colour coding denotes responsibility: grey bars indicate tasks conducted by all partners, orange bars those led by the computer science centres, and blue bars those led by the medical centres.

From month 7 through month 24, the focus shifts to development, integration and validation of the prototype ML- and DL-based predictive prognostic models. Retrospective data will be used to train separate ML and DL models aimed at predicting the spread of GB recurrence. These models will be refined iteratively and integrated into a unified framework of prototype ML- and DL-based predictive prognostic models, which will then be applied to prospective data as it becomes available.

Concurrently, an automated segmentation software prototype will be deployed and optimized throughout this period. All software components, from preprocessing pipelines to the predictive prognostic models and segmentation modules, will undergo continuous testing and improvement.

### Study population and sample size

We will retrospectively identify all consecutive patients with histologically confirmed aggressive high grade glioma who experienced a recurrence and underwent treatment between January 2014 and December 2020.

This time frame was selected to ensure an adequate follow-up duration for most patients, allowing for meaningful analysis of recurrence patterns and survival outcomes. Based on institutional records, approximately 200 patients are expected to meet the initial screening criteria.

Enrollment will be based on the following inclusion criteria (Figure 2):

Histopathological diagnosis of glioblastoma or diffuse astrocytoma, reclassified according to the 2021 WHO CNS tumor classification:

i IDH-wildtype glioblastoma (CNS WHO grade 4), orii IDH-mutant astrocytoma, grade 4.

Availability of molecular markers (IDH mutation status, MGMT promoter methylation, etc.), when tested.Radiologically or histologically confirmed recurrence.Sufficient clinical and radiological follow-up, defined as a minimum of 24 months or until documented disease progression or death.

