**Figure 2 fig2:**
[figure not shown]
Study flowchart showing patient selection, inclusion/exclusion criteria, and outcome analysis. IDH, isocitrate dehydrogenase; MGMT, O6-methylguanine-DNA methyltransferase; PFS, progression-free survival; OS, overall survival.

By including cases up to December 2020, we ensure a follow-up window extending at least to 2024–2025, which is crucial given the potential for long survival in patients with IDH-mutant tumors.

Needle biopsies, second surgeries, and patients lost to follow-up will be excluded. Calculating an approximate 30% dropout rate due to the exclusion criteria, we would enroll around 140 patients in the final analysis.

While traditional power calculations and formal sample size justifications are challenging for exploratory high-dimensional radiomic studies, a final cohort of approximately 140 patients is considered methodologically adequate for classical Machine Learning applications. To mitigate the risk of overfitting and directly address the potential class imbalance between local and distant recurrences, we will implement data augmentation and synthetic resampling techniques (such as the Synthetic Minority Over-sampling Technique, SMOTE) on the extracted radiomic features, ensuring robust and generalizable model training.

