### Analysis

Data analysis will be performed using ML and DL techniques, both of which fall under the broader field of AI and supervised pattern recognition (10, 11).

ML is a well-established approach that involves algorithms capable of processing and learning from data without being explicitly programmed. Once trained, these algorithms can apply the learned patterns to make data-driven predictions. A typical ML workflow includes several sequential stages: data acquisition and preprocessing, computation of a large number of variables (also referred to as features or attributes, which may be either domain-specific or domain-agnostic), dimensionality reduction, model training and validation, and eventual deployment (12). During training, the ML model identifies patterns and correlations between features and the outcome variable of interest, aiming to generalize this knowledge and accurately predict outcomes even in previously unseen cases.

DL represents a more recent advancement within ML, offering a key advantage in its ability to automatically learn complex, high-level features directly from the data. Unlike traditional ML approaches, which require manual feature engineering by domain experts or extensive trial-and-error processes, DL models progressively extract informative representations in an automated and hierarchical manner. This significantly reduces the dependency on prior domain knowledge and manual intervention in feature selection.

The goal of the ML and DL classification approaches will be to predict the spread of GB recurrence, based on preoperative clinical, radiological, and instrumental data. These models aim to classify patients according to expected recurrence patterns, such as local versus distant regrowth, and provide spatial forecasts that can support surgical planning and treatment personalization.

Data analysis will be conducted using Python and Matlab environments. The computational framework will rely on the integrated and multivariate analysis of features derived from both clinical and imaging data collected during the pre-operative periods.

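### Two WHO diagnoses are pooled in one classifier but the claims are made for glioblastoma, so the pooled AUC can partly reflect tumour type if distant-recurrence rates differ by IDH class

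*Protocol article*

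**What the plan says.** **Who is eligible.** Under Study population and sample size, the source population is patients with "histologically confirmed aggressive high grade glioma who experienced a recurrence". Diagnoses are reclassified by the 2021 WHO scheme, and two alternatives are accepted: "IDH-wildtype glioblastoma (CNS WHO grade 4") or "IDH-mutant astrocytoma, grade 4". Molecular markers, including IDH status, are required only where they were tested.

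**What is claimed.** The abstract's methods paragraph says that data collection "will be performed for all eligible GB patients". Under Analysis: "The goal of the ML and DL classification approaches will be to predict the spread of GB recurrence". The Study design section and the Conclusion also speak of GB.

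**How the types are analysed.** Radiological parameters and Primary outcome define one binary outcome, local or residual against distant, for the whole cohort. Neither separates the two diagnoses. Performance is judged by ROC curves, sensitivity and specificity; the abstract lists AUC first among its measures.

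**What the article says about the difference.** The text after Figure 2 calls the long follow-up window "crucial given the potential for long survival in patients with IDH-mutant tumors".

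**The concern.** By the classification the protocol adopts, the second eligible diagnosis is not glioblastoma. If the plan is followed as written, a result from a mixed cohort will be presented as a result about GB.

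This matters for an AUC in particular. A pooled AUC averages over every pair of one distant and one local case, including pairs in which one patient is IDH-mutant and the other IDH-wildtype. If the classes have different distant-recurrence rates, a model that knows the class ranks those mixed pairs well without any skill among glioblastoma patients. The nested cross-validation does not remove this. It prevents leakage between training and test folds, but the difference between diagnoses is present in every outer fold.

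The question asked is how well spread can be predicted in a patient with glioblastoma, and the pooled figure may look better than the answer to that question.

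**Working it through.** **1. The cohort figure.** 200 × (1 − 0.30) = 140, which reproduces the stated size.

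**2. Can the model see IDH class?** The places point in different directions.
- The abstract names pathological variables among those collected.
- Data collection lists biomolecular markers. Analysis then takes clinical features from the Data collection and Radiological parameters sections.
- Data collection is not in itself a list of predictors, because it also contains the outcome (type of recurrence) and the time to relapse.
- Elsewhere, Analysis restricts prediction to preoperative data. Tissue markers obtained at surgery would not obviously qualify.

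So markers may enter as features, and the article does not settle whether they do.

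**3. Assumed inputs.** None of these is in the article: AUC 0.60 within each class, 20% distant in IDH-wildtype, IDH-mutant share 5, 10 or 15%, and distant rate in mutants 5, 20, 30 or 50%.

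**4. Formula.** Take a binormal score with separation d = √2 × Φ⁻¹(0.60) = 0.358, so d² = 0.128, and add the class log-odds. With Δ the log-odds of distant recurrence in mutants minus that in wildtype:
- a pair from the same class is ranked correctly with probability 0.60;
- a distant mutant against a local wildtype: Φ[(d² + Δ)/(d√2)];
- a distant wildtype against a local mutant: Φ[(d² − Δ)/(d√2)].

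The pooled AUC is the average of these, weighted by how often each pair occurs.

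**5. Worked case: 15% share, 50% distant in mutants.**
- Distant: wildtype 0.85 × 0.20 = 0.170; mutant 0.15 × 0.50 = 0.075. Mutant fraction 0.075/0.245 = 0.306.
- Local: wildtype 0.85 × 0.80 = 0.680; mutant 0.075. Mutant fraction 0.075/0.755 = 0.099.
- Δ = 0 − (−1.386) = 1.386. Mixed-pair probabilities: Φ(2.99) = 0.9986 and Φ(−2.48) = 0.0065.
- Pooled AUC = 0.694 × 0.901 × 0.60 + 0.306 × 0.099 × 0.60 + 0.306 × 0.901 × 0.9986 + 0.694 × 0.099 × 0.0065 = 0.375 + 0.018 + 0.275 + 0.000 = 0.669.
- The AUC within IDH-wildtype is still 0.60, so inflation is 0.069.

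**6. Range.** Pooled AUC, with inflation over 0.60 in brackets:

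| Distant rate in mutants | 5% share | 10% share | 15% share |
|---|---|---|---|
| 5% | 0.616 (0.016) | 0.631 (0.031) | 0.645 (0.045) |
| 20% (equal) | 0.600 (0) | 0.600 (0) | 0.600 (0) |
| 30% | 0.606 (0.006) | 0.610 (0.010) | 0.614 (0.014) |
| 50% | 0.628 (0.028) | 0.651 (0.051) | 0.669 (0.069) |

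**7. Precision of a GB figure.** IDH-wildtype patients number 140 × 0.95 = 133 down to 140 × 0.85 = 119, if all are tested. The Hanley–McNeil variance is [A(1−A) + (n₁−1)(Q₁−A²) + (n₀−1)(Q₂−A²)]/(n₁n₀), with Q₁ = A/(2−A) and Q₂ = 2A²/(1+A). Assume A = 0.70 and 20% distant. For all 140 patients (28 distant, 112 local) the variance is (0.210 + 1.309 + 9.598)/3136 = 0.00354, and the 95% half-width is 1.96 × 0.0595 = 0.117. For 133 to 119 patients it is 0.120 to 0.127.

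**The case against.** **The rates may not differ.** Nothing in the article says that site of recurrence depends on IDH class. The remark about long survival concerns the follow-up window. This stands: with equal rates the inflation is zero.

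**The model may not see the class.** If the preoperative restriction is taken literally, markers are not inputs, and class information could reach the model only indirectly through other features. The calculation gives the model exact knowledge of class and its effect, so indirect learning would yield less. This also stands as a limit on size.

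**The effect is small beside sampling noise.** A repeat at n = 140 used a two-predictor ridge logistic model and stratified 5-fold cross-validation, with 600 runs per setting. The mean gap between pooled and wildtype AUC was 0.00–0.01 for a mutant distant rate of 30%. For a rate of 50% it was 0.02, 0.05 and 0.06 at shares of 5, 10 and 15%. The run-to-run SD of the pooled AUC was 0.07–0.09. That is fair about size. Where rates differ by class, however, the gap is a systematic shift in what is being estimated, and wide intervals do not correct it.

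**Subgroup tables belong in a fuller document.** Agreed, and the absence of one is not the point. The eligible population and the population of the claims disagree in this text.

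**Pooling is legitimate and disclosed.** Both types are listed openly, the Discussion treats heterogeneity as a strength, and the Conclusion calls the work exploratory. A reader might infer that IDH-mutant cases should be excluded. The article does not support that: a grade 4 glioma cohort is a valid target if it is named as one.

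**Conclusion.** The mismatch stands on the text alone: two diagnoses under the protocol's own classification, one classifier, and claims for only one of them. It limits what the results can say about GB and should be corrected before they are seen.

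The effect on the AUC is a possibility that depends on two conditions: the model has IDH class or a good proxy for it, and distant-recurrence rates differ by class. Under the assumed inputs, inflation runs from 0, through about 0.01 for a modest difference, to about 0.07 at the extreme examined. A reader might infer that the published AUC will be inflated by several hundredths. The documents do not support that, because they give neither the IDH-mutant share nor the rates by class, and they leave open whether markers are features.

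**What to change.** - Keep all patients in training.
- From the same outer-fold predictions, report AUC, sensitivity and specificity in IDH-wildtype patients, and make this the result that supports any statement about GB.
- Give the pooled figure beside it, labelled as grade 4 glioma, both IDH classes.
- Count patients without IDH testing only in the pooled figure, since they cannot be assigned to either diagnosis.
- State whether biomolecular markers are model features, so that the feature description and the preoperative restriction in Analysis agree.

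**Cost.** No new data, no refitting and no loss of training patients. The GB interval is slightly wider: a half-width of about 0.120–0.127 against 0.117 under the assumptions above, and wider still if many patients were never tested for IDH.

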**Figure 2 fig2:**
[figure not shown]
Study flowchart showing patient selection, inclusion/exclusion criteria, and outcome analysis. IDH, isocitrate dehydrogenase; MGMT, O6-methylguanine-DNA methyltransferase; PFS, progression-free survival; OS, overall survival.

By including cases up to December 2020, we ensure a follow-up window extending at least to 2024–2025, which is crucial given the potential for long survival in patients with IDH-mutant tumors.

Needle biopsies, second surgeries, and patients lost to follow-up will be excluded. Calculating an approximate 30% dropout rate due to the exclusion criteria, we would enroll around 140 patients in the final analysis.

While traditional power calculations and formal sample size justifications are challenging for exploratory high-dimensional radiomic studies, a final cohort of approximately 140 patients is considered methodologically adequate for classical Machine Learning applications. To mitigate the risk of overfitting and directly address the potential class imbalance between local and distant recurrences, we will implement data augmentation and synthetic resampling techniques (such as the Synthetic Minority Over-sampling Technique, SMOTE) on the extracted radiomic features, ensuring robust and generalizable model training.

### Data collection

For each enrolled patient, we will extract clinical and imaging parameters from electronic medical records. Demographic and clinical variables will include age, tumor localization and laterality, presence of residual tumor after surgery, type of adjuvant treatment, type of recurrence (local or residual, distant, or combination), delay of relapse and biomolecular markers of the tumor.

